In addition, response training is of great significance in ameliorating cognitive impairment and delaying the occurrence of dementia and Alzheimer disease [10]. People with different physical abilities may receive different results from reactivity training. Previous studies have found that the plasticity of the brain can change, particularly among professional athletes who have received extensive physical training [11-13]. In particular, volleyball players performed better in the implementation of control tasks and visual-spatial attention processing tasks. The action observation network plays an important role in these tasks, with the upper parietal lobe and auxiliary motor area being positively correlated with anticipatory capacity [14,15].

However, most forms of exercise are not suitable for the older population due to physical limitations. Therefore, the design and development of a combination of muscle and balance function training is an effective way to improve muscle coordination, prevent falls, and improve the cognitive state of older people. With advancements in technology, cognitive training equipment used in the community or by families is being widely used, which can better meet the issues of accessibility and portability of cognitive training. This study uses smart equipment to train the visual-motor response abilities of volleyball players, ordinary college students, and older people. We use functional magnetic resonance imaging (fMRI) to visualize the characteristic brain regions involved in perception of movement across different physical functions and explore the effects of cognitive training on cognitive function and the mechanisms of brain plasticity. The aims of this study are as follows: (1) to compare the functional advantages and characteristics of the brain perceptual-motor system in volleyball players and ordinary younger and older people; (2) to explore the influence of visual-motor response ability training on cognitive function in people with different physical functions; and (3) to preliminarily confirm the efficacy and safety of exercise-based nondrug therapy in improving cognitive function.

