### Intervention

The implementation team of the intervention process includes a sports rehabilitation physician, a neurologist, a volleyball coach, a graduate student, and 2 undergraduate students. Before the formal intervention, the researchers were made familiar with the intervention equipment and intervention process through training. A between-group control design will be used with the same interventions. The 3 groups of participants will receive the same visual-motor response training for 30 minutes a day over 14 days. Response training will be completed with the help of gForceDual equipment and Neuro Rehab System (OYMotion). The participants download the Neuro Rehab System–based app and connect the gForceDual device to their mobile device through Bluetooth. During each training session, the gForceDual equipment will be secured to the transverse striation of the distal wrist of the participants’ right upper limb, and its electrode will be attached to the ventral part of the palmar longus muscle, brachioradialis muscle, radial carpal flexor muscle, and ulnar carpal flexor muscle. The response sensitivity will be adjusted via the app, and the participants will be guided by visual information to carry out wrist dorsal extension and flexion. The speed adjustment function in the app will be set to divide the training speed into gears, with a total of 10 gears. The default setting is sixth gear during the intervention. If an older person cannot keep up with the response, the app will downshift through gears; conversely, if an athlete can adapt well to a high gear, the app will upshift the gear. The researchers will record electromyographic signals produced by dorsal extension and flexion of the wrist.

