### Statistical Analysis

All variables that can be measured directly will be analyzed descriptively by tabulating the empirical distributions. For continuous variables, mean (with SD), median, minimum, and maximum values will be documented. Classification variables will be recorded as incidence and percentage. Measurement data following a normal distribution will be analyzed with a 2-way repeated measures ANOVA. For intergroup factors, the participants will be divided into 3 groups, comprising athletes, young people, and older people. The intragroup factor will be evaluation time, which has 2 levels—before and after the intervention. The main effects and interactions among the 3 groups will be analyzed. For nonnormally distributed data, the Wilcoxon symbolic rank test will be used for intragroup analysis, and the Mann-Whitney *U* test will be used for intergroup comparison. The significance level of the statistical test is set at α=.05, and bilateral tests will be carried out. Differences in classification variables will be calculated using the *χ*^2^ test. *P*<.05 will be considered statistically significant.

The differences in brain fMRI images will be analyzed by MATLAB (R2014a; MathWorks) and Statistical Parametric Mapping (version 12; UCL Queen Square Institute of Neurology) [24]. Based on the intergroup analysis of the resting-state amplitude of low-frequency fluctuations (ALFF) and regional homogeneity (ReHo) indices, we will perform a flexible-design ANOVA to characterize the individual samples at each time point. Analyses will include time main effects, grouping main effects, time × grouping interactions, and statistical parameter diagrams. The post hoc test mask will reflect differences in brain regions where *P*<.01 and voxel >10, as determined by the ANOVA results. The intergroup analysis of functional connections will be done using GRETNA (Neuroimaging Tools and Resources Collaboratory) [25]. The functional connection differences among the 3 groups will be analyzed with a 2-factor repeated measurement ANOVA, and the intragroup analysis will be conducted with a paired 2-tailed *t* test. A *P* value <.01 is considered to show statistical significance. BrainNet Viewer (Neuroimaging Tools and Resources Collaboratory) will be used to draw schematic maps of brain regions with significant differences.

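### The grouping main effect for ALFF and ReHo averages pre- and post-training scans, and depending on an unstated model setup it may also be tested against too small an error; aim 1 is better tested on baseline maps

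*Protocol article*

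**What the plan says.** In the protocol article, Statistical Analysis, the resting-state ALFF and ReHo maps are to be analysed with "Statistical Parametric Mapping (version 12; UCL Queen Square Institute of Neurology"). The model is given in one clause: "we will perform a flexible-design ANOVA to characterize the individual samples at each time point". The effects to be taken from it follow: "Analyses will include time main effects, grouping main effects", and then the time × grouping interaction and statistical maps. A post hoc mask is then built from the ANOVA results at P<.01 and more than 10 voxels.

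For the behavioural data, the same section defines the factors: "the participants will be divided into 3 groups, comprising athletes, young people, and older people", and "The intragroup factor will be evaluation time, which has 2 levels—before and after the intervention". The fMRI paragraph uses the same two factors, time and grouping.

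Under Intervention, "The 3 groups of participants will receive the same visual-motor response training for 30 minutes a day over 14 days". Every second scan is therefore a post-training scan.

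Aim 1 in the Introduction is "to compare the functional advantages and characteristics of the brain perceptual-motor system in volleyball players and ordinary younger and older people". The Discussion (Principal Findings) states the matching hypothesis: people with long exposure to this kind of training have a functional advantage over the general population.

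**The concern.** There are two separate issues with one line of the plan.

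The first concerns what is estimated. The hypothesis behind aim 1 is about a difference that exists before the study's own training begins. The baseline scan measures that. A grouping main effect in a group × time model measures something else, the group difference averaged over both scans. If athletes, students and older adults respond differently to two weeks of training, which aim 2 sets out to explore, part of that response is counted as a group difference.

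The second concerns the error against which it is tested. A repeated-measures model with a subject factor and one residual per voxel has only within-subject error available. That suits time and time × group. For a between-subject effect it is too small whenever a person's two scans are positively correlated, and the voxelwise test then rejects too often. The article does not state the subject factor or how the pre-post covariance is handled, so this part depends on the setup.

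At stake is the credibility of any map reported as an athlete advantage, and of the mask that decides where post hoc comparisons are made. The 3-group F also mixes ages 18–23 with 55–70, so it may be driven largely by age, although it responds to an athlete–student difference too.

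**Working it through.** The plan gives no operating characteristic for this test, so there is no figure of its own to reproduce.

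**Inputs**
- From the protocol: 3 groups; 2 time points; 20 per group as the planned number (Sample Size); threshold P<.01.
- Assumed: the correlation ρ between a person's two scans at a voxel. The document gives none, so a range is shown.
- Assumed: the model setup, because subject factor and covariance handling are not stated. Three setups are shown.

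**Step 1: what the grouping main effect estimates**

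Let B be the baseline difference between two groups and C the difference between their pre-to-post changes. The post-training difference is B + C, and the main effect is

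[B + (B + C)] / 2 = B + C/2.

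- If C = 0, it equals B and there is no bias.
- If B = 0 and one group alone gains 0.5 SD, it is 0.5/2 = 0.25 SD.

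Size of the second case with the correct between-subject error: a subject mean has SD √((1+ρ)/2), so f = 0.25·(√2/3)/√((1+ρ)/2) and λ = 60f².
- ρ = .5: f = 0.136, λ = 1.11; rejection 13.8% at nominal 5% and 4.1% at nominal 1%.
- ρ = .7: f = 0.128, λ = 0.98; rejection 12.7% and 3.7%.

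So training alone can produce a group finding with no baseline difference, though only modestly for a gain of this size.

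**Step 2: error term, subject factor with a single residual**

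Under no group difference, with variance σ² per scan:
- expected group mean square = σ²(1+ρ)
- expected within-subject residual = σ²(1−ρ)

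The ratio is inflated by (1+ρ)/(1−ρ). The true rejection rate is P(F(2,57) > Fcrit·(1−ρ)/(1+ρ)), with Fcrit = 5.00 at 1%.

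| ρ (assumed) | inflation | effective cut-off | false-positive rate at nominal 1% |
|---|---|---|---|
| .3 | 1.86 | 2.69 | 7.6% |
| .5 | 3.00 | 1.67 | 19.8% |
| .7 | 5.67 | 0.88 | 42.0% |

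At ρ = 0 there is no inflation. A simulation of 20,000 null data sets at ρ = .6 gave 29.6% (formula 29.4%). The same data tested against between-subject error gave 0.9%. With 26 per group the three rates are 7.8%, 20.2% and 42.5%, so sample size hardly matters.

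**Step 3: the other two setups**
- No subject factor, scans treated as independent: the error pools both strata, with expectation σ²[(1+ρ)+(1−ρ)]/2 = σ², so the inflation is only 1+ρ. By Monte Carlo the rate at nominal 1% is 2.8% (ρ = .3), 4.5% (.5), 6.5% (.7) and 8.7% (.9).
- No subject effects, pre-post covariance estimated: about nominal.

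**Step 4: effects not touched**

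In the subject-factor setup, time and time × group are within-subject effects and are tested against the right error.

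**The case against.** A reader might infer that the plan uses the wrong error term and that aim 1 will be full of false positives. The text does not support that. It names a flexible-design ANOVA in SPM12 and stops there. Factor lists and covariance settings are details that an article commonly leaves to a fuller document, and one setup compatible with the wording is about right. This objection stands, so the error-term part is conditional and the 42% figure is one branch at one assumed correlation.

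The article never says that aim 1 rests on the grouping main effect, and its phrase about characterising samples at each time point could cover a baseline comparison. That is fair. The link is an inference, but a natural one: no baseline-only contrast appears among the listed effects. Functional connectivity and the behavioural measures have their own analyses, which the SPM error-term point does not reach.

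The primary outcome is a before-after difference, so it rests on time and time × group. In the subject-factor setup these are sound.

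A reader might also infer that the 3-group mask confines athlete–student comparisons to age-driven regions. That goes too far. The mask comes from the ANOVA results, which include time and interaction effects, and the group F itself responds to an athlete–student difference.

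Finally, averaging does harm only if groups respond differently, and the study calls itself exploratory. Both are true. Neither makes an average of trained and untrained scans a good measure of a pre-existing difference.

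**Conclusion.** The averaging point holds under any model setup: the listed grouping effect estimates B + C/2, not B. Its bias is half the group difference in training change, and zero if the groups change alike.

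The error-term point holds only conditionally. At nominal 1% with 20 per group, the rate is about 8% to 42% for ρ from .3 to .7 with a subject factor and single residual, about 3% to 9% for ρ from .3 to .9 with scans treated as independent, and about nominal with the covariance modelled and no subject effects. Both ρ and the setup are assumptions. The case for change does not depend on settling which setup applies, because the remedy is valid under all of them. This is a worthwhile and inexpensive improvement. It does not show that the planned results will be invalid.

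**What to change.** Replace the single list of effects with three stated tests per index (ALFF, ReHo):
- **Aim 1:** one-way ANOVA across the 3 groups on baseline maps only, with an athletes-versus-students contrast planned in advance and not restricted to the omnibus mask. These two groups share the 18–23 age range.
- **Group × time:** one-way ANOVA on each person's post-minus-pre map.
- **Time:** one-sample t test on the post-minus-pre maps.

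State that the grouping main effect from the flexible-design model will not be interpreted. Each replacement has one map per person, so its residual is the correct error without further settings.

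The change needs new analysis wording, with the same data and software. The article reports recruitment complete as of September 11, 2024, with data collection and analysis still to finish. The cost is probably fewer significant group differences, plus some precision for aim 1: a baseline-only group mean has variance σ²/n against σ²(1+ρ)/(2n) for the two-scan average, a ratio of 2/(1+ρ), or 1.33 at ρ = .5 and 1.18 at ρ = .7.

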### Sample Size

Because of the exploratory nature of this study, it is impossible to estimate the total number of cases. Based on previous data, fMRI studies can be performed in groups of 12 participants with adequate statistical efficacy [16]. For the planned number of 20 participants in each group, if a 1-way ANOVA is used, it will be possible to detect a standardized mean-value effect (Cohen *d*) of 0.4, with a power of 80% and a significance level of 5% [17,18]. Assuming a loss to follow-up of 20%, the total sample size required for the study is 78 (n=26 in each group).

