### Outcome Measures

The aim of the study is to explore the functional characteristics of brain perceptions of movement and the cognitive changes in different groups after response ability training. The primary outcome is defined by differences in fMRI images of characteristic areas of the brain before and after the intervention. A Siemens Magnetom Verio 3.0T MRI system will be used for scanning before and after the intervention.

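### The fMRI rule (voxel P<.01 with more than 10 voxels; connectivity P<.01) states no correction over voxels, clusters or connections, and does not control whole-brain error at common smoothness

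*Protocol article*

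**What the plan says.** All references are to the protocol article.

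- **Outcome Measures:** "The primary outcome is defined by differences in fMRI images of characteristic areas of the brain before and after the intervention". No region is named.
- **Statistical Analysis, indices and effects:** the image analysis uses "resting-state amplitude of low-frequency fluctuations (ALFF) and regional homogeneity (ReHo) indices". For these, "Analyses will include time main effects, grouping main effects, time × grouping interactions, and statistical parameter diagrams".
- **Statistical Analysis, region rule:** "The post hoc test mask will reflect differences in brain regions where *P*<.01 and voxel >10, as determined by the ANOVA results".
- **Statistical Analysis, connectivity:** a two-factor repeated-measures ANOVA compares the groups, and "the intragroup analysis will be conducted with a paired 2-tailed *t* test". The criterion is: "A *P* value <.01 is considered to show statistical significance".
- **Statistical Analysis, non-imaging variables:** "The significance level of the statistical test is set at α=.05, and bilateral tests will be carried out". This says nothing about multiple testing in the images.

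The section states no family-wise, false-discovery, random-field or permutation correction for any of these analyses.

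**The concern.** A voxel threshold of P<.01 applies to one voxel at a time. Over tens of thousands of voxels, many pass by chance, and because images are smooth the chance voxels form clumps. A minimum extent protects the map only if it is large relative to the smoothness of the data. An extent fixed at 10 voxels, whatever the voxel size, smoothness and search volume, has no known error rate. The connectivity threshold has the same weakness across edges.

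This matters because the rule governs the trial's main outcome. If training changed nothing, the plan could still yield regions reported as showing brain plasticity, and the reader could not tell these from real ones. The numerical thresholds are written into the article, so this is a rule that is badly fixed and not a detail left to a later document.

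**Working it through.** **Inputs from the article.** Three groups; 20 evaluable per group ("For the planned number of 20 participants in each group, if a 1-way ANOVA is used"); voxel P<.01; more than 10 voxels; two indices and three effects, so 2 × 3 = 6 ALFF/ReHo maps. Of these, time and time × group give 2 × 2 = 4 maps on before-after change. The article gives no error rate for the rule, so there is no figure to reproduce.

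**Inputs assumed.** Voxel size, mask, smoothness (FWHM) and number of nodes.

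**Step 1: false voxels.** In a mask of 85,544 voxels of 3 mm, the expected number passing by chance is 0.01 × 85,544 ≈ 855 per map. The question is how often they clump into more than 10.

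**Step 2: false clusters.** Null simulation of the time × group test: smooth Gaussian noise for 3 × 20 difference maps, F(2,57) at P<.01, 18-neighbour clusters, 60 runs per setting.

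| FWHM (mm) | At least one cluster >10 voxels | Mean false clusters | Extent holding map error near 5% (voxels) |
|---|---|---|---|
| 4 | 0% | 0.0 | 8 |
| 5 | 40% | 0.5 | 14 |
| 6 | 97% | 4.3 | 22 |
| 8 | 100% | 18.1 | 45 |
| 10 | 100% | 24.1 | 85 |
| 12 | 100% | 25.1 | 139 |
| 15 | 100% | 20.4 | 248 |

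The last column is the 95th percentile of the largest null cluster.

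Two further sets of runs agree:

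- About 76,000 voxels: false clusters in 30 of 30 maps at both 6 and 8 mm (means 4.0 and 15.4).
- About 81,000 voxels, covering both the 2-df interaction and the 1-df time effect: 12 of 12 at 6 and 8 mm, 50-75% at 5 mm, 0 of 12 at 4 mm.

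Across all runs the mean is about 3-6 false clusters at 6 mm and 15-18 at 8 mm. The runs are few: the standard error of the 40% figure is √(0.4 × 0.6/60) ≈ 6 percentage points, and 12 of 12 is compatible with a true rate as low as 0.05^(1/12) ≈ 78% (one-sided 95% bound).

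**Step 3: sensitivity.**

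- 26 per group at 8 mm: 100%.
- 2-mm voxels at 4 mm: 100% (30 runs).
- Mask of about 10,000 voxels: 40% at 6 mm, 85% at 8 mm.
- 40% per map, if maps were independent: 1 − 0.6⁴ = 87% over the four before-after maps and 1 − 0.6⁶ = 95% over all six.

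**Step 4: connectivity.** With r nodes there are m = r(r − 1)/2 edges. The expected number of false edges per effect is 0.01m. The familywise error under independence is 1 − 0.99^m.

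- r = 10: m = 45, error 36%.
- r = 20: m = 190, error 85%.
- r = 90: m = 4,005, about 40 false edges, error close to 100%.

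The expected count does not need independence. Bonferroni for 4,005 edges would be 0.05/4,005 ≈ 1.25 × 10⁻⁵.

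**Step 5: post hoc tests in the mask.** A voxel enters the interaction mask if F(2,57) > 4.998. With three equal groups and a pooled error, the most extreme pair has t² of at least 3/4 of the between-group sum of squares over the error mean square. That ratio is 2F, so t² ≥ 1.5F > 7.50 and |t| > 2.74, which on 57 df is P ≤ .0082. Multiplied by three pairs, this is P ≤ .025. So at least one pair passes at unadjusted P<.01 in every voxel selected, true or false. The post hoc step cannot remove a false voxel, and the observed differences there are large because they were selected to be.

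**The case against.** Four points can fairly be made for the plan.

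1. **The article never says its P values are uncorrected, and the quoted sentence defines a mask and not a declaration of significance.** Both are true. The absence of correction is inferred from silence, and the criterion for the ALFF/ReHo post hoc tests is not given. But a plain voxel P with a fixed small extent is what is written, and Step 5 shows why testing inside the mask does not repair it.

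2. **A reader might infer that false regions are virtually guaranteed.** The documents do not support that without conditions. The rate is near 0% at 4 mm smoothness on 3-mm voxels and 40% at 6 mm in a small mask. The outcome definition refers to characteristic areas, so a restricted search is not excluded, although none is specified. The count of 40 false edges is likewise a scenario: with 10 regions the familywise error is 36%.

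3. **A reader might count every index and all three effects as primary.** The outcome is defined by before-after differences. The group main effect is not such a difference, and functional connectivity is never named as primary. A global null is also a poor benchmark for comparing people aged 18-23 with people aged 55-70.

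4. **A reader might conclude that the primary result would have no evidential weight.** That goes too far. The Sample Size section calls the study exploratory, and Strengths and Limitations asks for better studies to follow. A lenient rule weakens claims about individual regions and does not void the whole result. The exploratory label is only a partial defence, because the Introduction also aims at preliminary confirmation of efficacy and the Discussion speaks of directly testing hypotheses.

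**Conclusion.** The concern holds in conditional form. The rule as written states no correction over voxels, clusters or connections, and its 10-voxel extent does not control whole-brain error at common settings. Assuming 3-mm voxels and a whole-brain mask, the null chance of at least one false cluster per map is about 0% at 4 mm, 40-75% at 5 mm and 97-100% from 6 mm upward. An extent that holds 5% at voxel P<.01 would be about 22 voxels at 6 mm and 45 at 8 mm. For connectivity, the result runs from about 36% familywise error (45 edges) to about 40 false edges per effect (4,005 edges). These sizes rest on assumed smoothness, voxel size, mask and atlas. Only the time × group and time effects were simulated. The direction is firm over most of the range examined, and nothing in the article confines the analysis to the settings where the rule would be adequate.

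**What to change.** - **ALFF and ReHo:** replace the rule with whole-brain cluster-level family-wise-error P<.05, for example with a voxel-forming threshold of P<.001 in SPM12, which the article already names, or a permutation-based equivalent. A larger extent at P<.01, calibrated to the estimated smoothness, could also hold the error rate. The essential change is that the extent follows from the data and is not fixed at 10.
- **Connectivity:** use FDR q<.05 or a network-based correction across connections.
- **Primary question:** state that the time and time × group effects carry the primary outcome, and treat the group main effect as descriptive.
- **Post hoc:** run pairwise tests only in surviving clusters with Holm adjustment, and report cluster-mean effect sizes as descriptive. These clusters are still selected from the same data, but the selection step then has a controlled error rate.

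The cost is lower sensitivity, so fewer regions will reach significance. No new data or participants are needed. The Results section describes data collection and analysis as still to be completed, so the rule should be fixed before results are seen.
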